### Interventions – Intervention group

The trial will attempt to reduce neonatal mortality in the intervention villages through a multi-level program: community health promotion and contracting out primary and secondary health services to non-public providers. All the services described below will be provided free to pregnant women and neonates in the intervention communities.

#### Community Health Promotion

To stimulate both adoption of healthy practices and demand for care, the trial will implement a concerted effort to promote health knowledge of communities in the intervention arm. The three main components of this are as follows:

• Training Village Health Workers and Midwives to deliver antenatal services

The trial will select and train local women in the intervention villages to serve as Village Health Workers (VHWs). The person selected as VHW will usually be an Auxiliary Nurse Midwife (ANM) or Traditional Birth Attendant (TBA) already resident in the village. The person chosen will be the most highly skilled available who is acceptable to the communities in the village.

The VHW will be extensively trained by doctors and other health professionals in domiciliary mother and baby care along with postnatal and infant care. They will also be trained in how to deliver antenatal care and conduct safe deliveries at home. They will make home visits to pregnant women and to mothers with neonates. They will also assist with home deliveries.

Approximately every two weeks, teams of two midwives will visit intervention villages offering a package of antenatal care and services (referred to below as "fixed-day services"). Midwives will be trained by doctors to deliver clear, correct pregnancy and neonate-related health information to mothers and their health care providers. They will be trained in community mobilization and the use of communication tools to address deep seated superstitions and practices that have negative impacts on the health of both mother and child. One midwife will act as the main medium for communication of sound health information to women in intervention villages. The other midwife will deliver antenatal health checks and identify high risk pregnancies. She will also give advice to the women, relatives and friends who accompany them on antenatal health care issues and birth planning.

These midwives will supervise VHWs, offer guidance, and conduct emergency deliveries if they occur during their visits to the villages. In case of complications, the midwife will be responsible for referring the mother/neonate in distress to the next level of care.

Midwives based in NPHCs will organise and oversee transportation for referred women.

The intervention team will train a total of approximately 250 VHWs (at least one for every village, in certain villages we may have to train more than one) and approximately 20 midwives (16 midwives delivering fixed day services in teams of two and 4 midwives based at NPHCs). They will go through a orientation program and training of not less than 10 days. This residential training will have both theoretical and practical components. It will be given by experts in the field of maternal and neonatal health care.

Additionally midwives will be trained to update a trial-specific health card provided to all eligible women in intervention villages. These cards will track the various services each woman in the intervention group has received under the programme, including immunizations, participation in health groups, regular checkups and hospitalisation. The VHWs and midwives will ensure that these cards are filled correctly and on time by the various health care providers. The midwives will also keep a record of the number of visits they have made to the village, the number of women they have met, the number of emergency deliveries with which they have assisted and the number of cases they have referred to the NPHCs. Midwives will also keep records of the nature of care they provide to each mother and child attended.

For reinforcement of messages, the VHWs and midwives will be given a manual to refer to for review. Regular meetings will be held to allow them to share knowledge regarding their work and problems encountered.

• Providing health education through a public information campaign

One of the most important contributors to poor maternal and neonatal health is a lack of good health information. This problem is particularly apparent in the local delivery and infant rearing practices which are often in contradiction of evidence-based good practice.

Health knowledge and awareness will be generated through frequent village meetings and community events. A health education campaign including theatre, films, focus groups and other media will be launched to promote key themes related to maternal and child health in each village. Folk culture in the form of song and dance will also be adapted to convey important messages to communities. All members of the community, not just women eligible for the trial, will be targeted by these campaigns.

As part of this campaign, VHWs will also make one to one contact through home visits with mothers, providing them with information related to their pregnancy and the health status of their child. These visits will be conducted on a periodic basis and will help reinforce good health care and practice in women and children. During fixed-day services, midwives will also answer health related queries that the women may have during the course of her pregnancy.

Midwives will also conduct regular village health meetings during the days on which fixed-day services take place. During these they will facilitate discussions, show films and use posters, flip charts and flash cards with the aim of promoting good health practices during and after pregnancy. The exact nature and duration of communication exposure will be designed by a health communications expert.

• Organising women's participatory discussion groups

As there is strong evidence that participatory women's groups can rapidly facilitate community-wide adoption of hygienic practices, a vital responsibility of the VHWs in intervention villages will be to facilitate good attendance at group discussions on issues related to maternal and neonatal health [6,7].

VHWs will organize eligible women from each village into participatory discussion groups of a maximum size between 15 and 20 individuals, creating multiple groups if necessary to maintain appropriate group size. These groups will meet during the day when fixed-day services take part. The midwives will conduct these approximately 1–2 hour sessions at a time and venue suitable to a majority of the women. Each session will contain ice-breakers, a review of the last meeting's content, presentation of new themes, reinforcement of themes through activities, demonstrations, games and a small assignment. These discussions will also be a forum where women can encourage each other to access the trial services. Finally, the participatory group will also serve as a group that provides valuable feedback about the various interventions.

Content for these sessions will include discussion of risk factors for the baby and mother, safe delivery techniques, causes of any recent deaths of neonates and mothers in nearby regions, and other issues that are important in the villages. The objective of these meetings is to improve mothers' health knowledge, to encourage greater use of fixed day services and other available health services, to encourage safe delivery techniques and delivery of high risk babies at the referral centre, and to give mothers a forum to discuss solutions to important issues in maternal and newborn health. This approach has been shown to be very successful in a trial in Nepal [6].

#### Contracting out primary and secondary health services to non-public institutions

As outlined in the trial justification, the supply of primary health care in the trial area is inadequate. Required improvements to the public sector were estimated to be prohibitively expensive, and evidence suggests the private sector may be able to provide primary care which is superior to that provided by the public, and potentially at a lower cost [11].

To increase supply of health services, the trial's intervention will designate up to 5 NPHCs to provide primary and secondary level care, made accessible through enhanced emergency transportation. NPHCs will be selected which are equipped with sufficient infrastructure and human resources. It is imperative to provide women in the intervention arm with quality services which are otherwise unavailable or inadequate, as it is expected that the educational component of the intervention will lead to greater awareness of the need for health services, and thus greater uptake of these services.

The list of candidate NPHCs will be drawn-up based on professional capability, existing infrastructure, and public perception of the facility (public perception serves as a way to introduce community participation in the selection process and to render the process transparent). Tie-ups with such facilities will initially be for the period of 3 months after which a favourable review would lead to a 6 month renewal of the contract. Any kind of primary or secondary service that an expectant mother would require during her pregnancy and for one month of the life of her baby would be covered by these facilities. By virtue of the contractual agreement, these NPHCs would be expected to provide around-the-clock service, admission to the general ward, food for the patient and one attendant, drugs, and disposables.

This contract will be subject to a per-patient cost ceiling. A rigorous monitoring system will buttress against over-billing and over-provision of services by the NPHCs.

Transportation will not be part of this contracting system, but will be provided directly at the village level for pick-up and drop off of patients at the NPHCs.

A detailed third party assessment of the quality of the services by the NPHCs will be conducted periodically by a committee of health and other professionals.

### Interventions – Control group

As the control villages will not be offered the trial interventions unless and until they are shown to be effective, yet data collection will still be required in these villages, control villages will receive the Naandi Foundation's *Girl Child Support Programme *[21], which is a component of a larger "Ensuring Children Learn Programme" run by the Naandi Foundation in two other states of India. The *Girl Child Support *component will provide academic and material support to girls between the ages of six and nine. This intervention is aimed at creating opportunities for young girls to attend and remain in school.

It is anticipated that these interventions in the control group will have negligible impact on neonatal mortality. The fact that these interventions are being carried out, however, may improve the extent and quality of the data collected in the control villages.

### Duration

The trial will run over a period of three years.

### Enrolment – Trial site(s) and participants

The trial site is the Nagarkurnool division of Mahabubnagar district in the Indian state of Andhra Pradesh. The trial will involve only those villages in the division with a population of less than 2,500 people. This criterion was decided upon in light of the fact that larger villages and towns generally have better access to health services, lower neonatal mortality rates, and therefore less potential to benefit from the interventions. Under this criterion, a total of 464 villages will be eligible for the trial with a total population of approximately 300,000 people.

### Enrolment – Inclusion criteria

A woman is eligible for inclusion in the trial if she satisfies the following criteria: i) she is married and less than 50 years old, ii) she or her husband have not had a family planning operation, iii) she is resident in one of the 464 villages at the time of a baseline survey that is to be carried out immediately prior to randomization, and iv) she meets all conditions for consent outlined in the consent section. Once the baseline survey has been carried out and the eligible women enrolled, the only permitted addition to the trial will be those women who marry into a trial village. Women will not be added or removed from the list as a result of either temporary or permanent migration from the village at which they are initially registered.

Only those children of eligible women whose estimated date of delivery at enumeration is at least six months after randomization will be included in the trial. As training and establishment of services in intervention villages will require time to be achieved, this lag in measurement is necessary to ensure exposure to the intervention.

### Enrolment – Exclusion criteria

Women and their children will be excluded from the trial if the woman in question is unmarried, if she is aged 50 or over at the time of the baseline survey, if she or her husband went through a family planning operation, or if she refuses to participate in the baseline survey.

### Enrolment – Sources/methods of enlisting participants in trial

An enumerator will be identified and trained in each of the 464 villages. After training, this individual will compile a list of all eligible women in their village and carry out a baseline survey of all such women. The starting point for the list of eligible women will be the official list of residents held by the Anganwadi Worker for the village.

### Enrolment – Dealing with migration

The population of the villages eligible for the trial will not remain static over the duration of the trial. Migration will occur for a number of different reasons. These will include permanent migration (which is relatively rare), marriage into a trial village, and temporary migration. As mentioned above, those women who marry into one of the 464 eligible villages during the duration of the trial will be considered eligible for participation in the trial. Temporary migration includes seasonal migration for work, which is very common in the area under scrutiny, and selective migration in order to give birth in the village where the pregnant woman's mother lives. This selective migration is expected to be nearly universal for women expecting their first child, but much more limited for later deliveries. In addition, some women might migrate because of a wish to benefit from the services provided in intervention villages, although it is anticipated that this is very unlikely.

In total we anticipate that around two-thirds of the deliveries of women enrolled in the trial will take place in the village of enumeration. Of the remaining one third, some will move to a village of the same type as their initial village (control or intervention), some will move to a location beyond the scope of the study, and some will move from intervention to control or vice-versa. This migration poses several challenges to the design of, data collection in, and analysis of the trial.

Because it is anticipated that the benefits of the intervention programme will occur throughout pregnancy and not just at the time of delivery, the trial has been designed to compare neonatal mortality rates according to village of residence rather than village at which delivery takes place. This allows each woman's village to be specified prior to randomisation, which reduces the potential for bias. A structural bulwark will ensure that only those women who are resident in intervention villages at the time of enumeration (along with those who marry in) receive the programme of services. Operationally those women who move from a control to an intervention village pose potentially the greatest problem. These women would normally not have subsidised access to non-public health services. If such exclusions have a negative impact on trial activities and morale in particular villages, then exceptional provision of non-public care will be decided upon in a case-by-case basis by the supervisors.

### Enrolment – Losses to follow-up

Data will be collected on each pregnancy at the enumeration village. It is not anticipated that women who do not migrate will voluntarily withdraw from the trial. When a woman migrates this will be documented and data collected when she returns. Every effort will be made to record data from all women who are included at enumeration to ensure that bias due to migration-related loss of observations is kept to a minimum. Women who migrate beyond the scope of the trial will be sought out for information. In case of inability to locate an enumerated woman, we will interview two of her relatives for birth information. Nonetheless, it is recognised that migration will both reduce the observed effect of the intervention and lead to some loss of information. This has been taken into account in the statistical power calculation.

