### Sample size calculation

The sample size has been calculated to give 80% statistical power to show a reduction in neonatal mortality that is statistically significant using a conventional 2-sided significance level of 5% if the true effect of the package of interventions is to reduce neonatal mortality by 25%. We assumed 4.38% neonatal mortality in the control villages (and hence 3.29% neonatal mortality in the intervention villages), an average population of 659 per village, a birth rate of 23 per 1000 population (giving rise to an average of 38 births per village over a period of 2.5 years) and an intra-cluster correlation coefficient of 0.00644 [20,6]. Under these assumptions we require 330 villages to detect a 25% reduction in neonatal mortality.

In the trial area, however, women who are expecting their first child usually move back to their mother's village around one to three months before the expected date of delivery. This migration could reduce the measured effect of intervention if women move from control villages to intervention villages and vice-versa. According to the NFHS-2, 36% of all births are first births in Andhra Pradesh. We assume that 90% of these women temporarily migrate and on the basis of this that 8% of control women actually deliver in an intervention village, whilst 24% of intervention women will deliver in non-intervention villages (8% in control group villages and 16% in villages outside of the study area) [20]. Assuming that both groups incur half the benefits of the intervention, the expected neonatal mortality rates in the two groups become 4.34% and 3.42%. Under this scenario 464 villages will still give 80% statistical power to show a reduction in neonatal mortality that is statistically significant at the 5% level.

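### The protocol says loss of information from migration is in the power calculation, but that calculation allows only for a diluted effect, so the 80% assumes complete outcome data

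*Protocol article*

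**What the plan says.** The section Enrolment – Losses to follow-up describes how migrating women will be traced. It accepts that migration will have two consequences all the same: a smaller observed effect and missing data. It closes by saying that migration will "lead to some loss of information. This has been taken into account in the statistical power calculation".

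The Sample size calculation section starts from these rates: "We assumed 4.38% neonatal mortality in the control villages (and hence 3.29% neonatal mortality in the intervention villages"). The number of births comes from an average village population of 659 and a birth rate of 23 per 1000, "giving rise to an average of 38 births per village over a period of 2.5 years". With an intra-cluster correlation of 0.00644, this leads to 330 villages.

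The section then allows for migration. It takes 8% of control women to deliver in an intervention village and 24% of intervention women to deliver in non-intervention villages, 16% of them outside the study area. Both groups are given half the benefit. The rates become 4.34% and 3.42%, and the section concludes: "Under this scenario 464 villages will still give 80% statistical power to show a reduction in neonatal mortality".

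The section Enrolment – Trial site(s) and participants says that "a total of 464 villages will be eligible for the trial with a total population of approximately 300,000 people".

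**The concern.** The follow-up section names dilution and lost information together and says they have been dealt with in the power calculation. The sample size section shows an adjustment for dilution only. It contains no loss fraction, no inflation factor and no reduction in births per village. The 16% of intervention women expected to deliver outside the study area enter as births with a known outcome and half the benefit.

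If no allowance is hidden in the village counts, the protocol tells its readers that 80% power withstands a loss it expects but has not budgeted for. A statement about power that the calculation does not support should be corrected before others rely on it. There is also no way to make up a shortfall by recruiting, because the 464 villages are all those eligible under the current population limit.

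**Working it through.** **Inputs** (Sample size calculation section unless noted): two-sided 5% level; 80% power; rates 4.38% and 3.29% before migration, 4.34% and 3.42% after; intra-cluster correlation 0.00644; 659 people per village; 23 births per 1000; 2.5 years. Half the villages go to each arm (Abstract, Methods/Design).

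**1. Births per village.** 659 × 0.023 × 2.5 = 37.9, stated as 38. This is the demographic yield with nothing removed for loss.

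**2. Rates after migration.** The full benefit is 25%, so half is 12.5%.
- Control: 4.38% × (1 − 0.08 × 0.125) = 4.34%.
- Intervention: 4.38% × (0.75 + 0.24 × 0.125) = 3.42%.

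Both stated rates are recovered from dilution alone.

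**3. Stated village counts with zero loss.** Design effect = 1 + (38 − 1) × 0.00644 = 1.238. Villages = 2 × (births per arm under individual randomisation) × 1.238 / 38. Births per arm come from the usual two-proportion formula, with and without continuity correction.

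| Rates | Stated villages | Births per arm, corrected | Villages, corrected | Births per arm, uncorrected | Villages, uncorrected |
|---|---|---|---|---|---|
| 4.38% v 3.29% | 330 | 5,054 | 330 | 4,872 | 318 |
| 4.34% v 3.42% | 464 | 7,132 | 466 | 6,916 | 452 |

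Villages are rounded up to an even number. Before rounding, the corrected figures are 329.3 and 464.8. The corrected formula matches 330 and comes within two villages of 464. The uncorrected formula misses 330. The protocol does not name its formula, so the correction is an inference from this match.

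On the corrected formula, dilution accounts for the whole rise from 330 to 464.

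**4. Power at 464 villages if outcomes are missing.** The protocol gives no loss rate, so the rates below are assumptions. Let a fraction f of births have no outcome, equally in both arms, with villages of equal size. Then births per village m = 38 × (1 − f), the design effect is 1 + (m − 1) × 0.00644, and the effective number per arm is 232 × m / design effect. For f = 10%: m = 34.2, design effect = 1.214, effective number = 232 × 34.2 / 1.214 = about 6,537, against 7,120 with no loss.

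| Assumed loss | Power, corrected | Power, uncorrected |
|---|---|---|
| 0% | 79.9% | 81.1% |
| 1% | 79.6% | 80.8% |
| 3% | 78.9% | 80.2% |
| 5% | 78.2% | 79.5% |
| 10% | 76.4% | 77.8% |

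Without the correction, power reaches 80% at about 3.5% loss.

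**The case against.** The arithmetic in the sample size section is sound and its assumptions are in the open, so a careful reader can see that no loss was included. The fault is one over-broad sentence elsewhere. That is fair. It bears on severity, but the sentence is still incorrect: it joins two consequences of migration, and only one of them is in the calculation. Nor is this a detail left to a fuller document, because the article makes the claim itself and shows the calculation that contradicts it.

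Three stronger readings are tempting, and the document does not support them.

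- **That 80% is lost as soon as any birth is missing.** This holds only with the continuity correction, which is inferred. Without it, about 3.5% loss is absorbed. Even with it, 79.6% at 1% loss still rounds to 80%.
- **That the one third of deliveries expected away from the village of enumeration are lost outcomes.** They are not. Comparison is by village of residence (Enrolment – Dealing with migration), where permanent migration is described as relatively rare. Data are collected when a woman returns, women who leave the trial's scope are sought out, and two relatives are interviewed if she cannot be located (Enrolment – Losses to follow-up). Each pregnancy is followed to at least six weeks after delivery (Surveillance/data collection). Counting the 16% who deliver outside the study area as observed fits these arrangements.
- **That a null result could not be interpreted.** A shortfall of a few points would hardly change its reading, and the Analysis strategies section commits to a relative risk with a 95% confidence interval.

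**Conclusion.** The inconsistency is real. The follow-up section credits the power calculation with an allowance for lost information that it does not contain. The stated 80% is conditional on a known outcome for every eligible birth, with a margin between roughly nothing (79.9%) and about one point (81.1%), depending on the formula.

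The practical size cannot be fixed from the document, because no loss rate is given and active tracing may keep loss low. Under the assumptions of equal loss in both arms and equal village size, power falls by about 1.5 points at 5% loss and about 3.5 points at 10%. Nothing in the document shows that loss would reach those levels. The village counts and diluted rates need no correction. This is a wrong statement about the basis of the power figure, of moderate to minor severity.

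**What to change.** Limit the closing sentence of Enrolment – Losses to follow-up to effect dilution, so that it no longer says lost information is in the power calculation. In the Sample size calculation section, state that 464 villages give 80% power if an outcome is obtained for every eligible birth. Name the formula, and add the power over a range of loss labelled as assumed, for example 5% and 10%. If the team has its own expected loss after tracing, that figure should replace the illustrative ones.

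The cost is a wording change and a slightly less favourable stated power. The design, the number of villages and the analysis stay as they are.
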